### 9.4.4 SAFETY ANALYSES

The DCOC will detail reported intervention-related AEs and SAEs experienced by study participants and will summarize these by the intervention arm. The DCOC will present summary statistics for overall and by sites.

---

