### 8.3 ADVERSE EVENTS AND SERIOUS ADVERSE EVENTS

#### 8.3.1 DEFINITION OF ADVERSE EVENTS (AE)

An AE is defined as any untoward occurrence associated with the use of an intervention in humans, whether or not considered intervention related (21 CFR 312.32 [a]). Stable chronic conditions that present prior to enrollment and do not worsen are not considered AEs but will be accounted for in the participant's medical history. Exacerbation or worsening of pre-existing conditions are defined as AEs. Reported AEs will be reviewed and classified by the investigator. We will only record and track severe, serious, and AEs related to the study

intervention. Expected AEs are listed below (8.3.3.3). This study is only reporting AEs for the child participant due to the negligible risk to providers and caregiver participants.

---

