#### 8.3.3.1 SEVERITY OF EVENT

These are the guidelines to describe the severity of AEs:

**Mild.** Events require minimal or no treatment and do not interfere with the participant’s daily activities.

**Moderate.** Events result in a low level of inconvenience or concern with the therapeutic measures. Moderate events may cause some interference with daily functioning.

**Severe.** Events interrupt a participant’s usual daily activity and may require systemic drug therapy or other treatment. Severe events are usually potentially life-threatening or incapacitating. Of note, the term “severe” does not necessarily equate to “serious.”

---

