#### 8.3.4 TIME PERIOD AND FREQUENCY FOR EVENT ASSESSMENT AND FOLLOW-UP

The study team will collect severe AEs, SAEs, and AEs related to study procedures. The study team will provide participants with a site-specific telephone number to report AEs, but will not actively solicit AEs or SAEs. The occurrence of a SAE may come to the attention of study personnel during clinical visits, by the clinical team with administration of RAMP Reports, or by the medical monitor upon reviewing data. The site study team will capture all AEs on the appropriate case report form following the instructions and timelines provided in the MOP. Information to be collected includes event description, date/time of onset, date/time of resolution, clinician's assessment of severity, relationship to study intervention and time of resolution/stabilization of the event. Site study teams must follow all severe and SAEs, regardless of relationship, until there is resolution, the condition stabilizes, the event is otherwise explained or is judged by the protocol study team to be no longer clinically significant, or the participant is lost to follow-up.

Clinic providers participating in this study will be asked to remind caregiver participants to report any medication side effects or events that caused them to seek medical assistance or hospitalization for their child to the study team.

---

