#### 8.3.5 ADVERSE EVENT REPORTING

Site coordinators and/or the study team will record potentially related AEs and severe AEs in the electronic data capture (EDC) system, include them in the statistical analysis, and follow the reporting procedures outlined in the trial-specific MOP. The MOP section on reporting severe AEs will encompass the requirements of:

1. Reviewing IRB's policies and procedures
2. Standard Operating Procedures (SOPs) for the Streamlined, Multisite, Accelerated Resources for Trials IRB Reliance platform (SMART IRB)

3. ICH E6(R2), GCP: Integrated Addendum to ICH E6(R1): Guidance for Industry
4. Following local IRB's policies and procedures, when applicable. If there are discrepancies between the procedures, we will follow the most stringent of the procedures.

The DCOC will report severe AEs to the reviewing IRB for its yearly continuing review. The DCOC will report to the Central IRB (cIRB), as specified in the study-specific IRB communication plan, based on recommendations of the SMART IRB. Sites will also report severe AEs to the local IRB, per local IRB policies and procedures, and make them available to the sponsor (DCOC) on a continuing basis through the EDC system. The study team will report to the DSMB, per the DSMB charter.

The trial-specific MOP will describe the details of the reporting structure and additional details related to timelines for reporting.

The specific regulations of the FDA do not apply to this protocol because this is not an FDA-regulated trial.

---

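### The by-arm safety summary in Section 9.4.4 covers fewer events than Sections 8.3.1, 8.3.4 and 8.3.5 record and send to analysis; severe, non-serious, unrelated AEs are left out

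*Protocol*

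**What the plan says.** **What is recorded.** Section 8.3.1: "We will only record and track severe, serious, and AEs related to the study" intervention. Section 8.3.4 gives the same three categories: "The study team will collect severe AEs, SAEs, and AEs related to study procedures". It adds a follow-up duty that ignores causality: "Site study teams must follow all severe and SAEs, regardless of relationship". Section 8.3.6 has all SAEs entered in the EDC, with no causality limit.

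**What goes to analysis.** Section 8.3.5 says that sites and the study team will "record potentially related AEs and severe AEs in the electronic data capture (EDC) system, include them in the statistical analysis".

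**What is summarized.** Section 9.4.4: "The DCOC will detail reported intervention-related AEs and SAEs experienced by study participants". The same sentence has these summarized by arm. The section also promises summary statistics overall and by site. No other part of Section 9 covers adverse events.

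**Severe and serious.** Section 8.3.3.1 says that the term severe "does not necessarily equate to" serious, although it also says: "Severe events are usually potentially life-threatening or incapacitating".

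**The concern.** Section 9.4.4 does not name severe AEs. A severe event that meets no seriousness criterion and is judged unrelated to RAMP therefore satisfies the recording rule and the Section 8.3.5 commitment, but has no place in the summary that reports safety by arm. A SAP author who follows Section 9.4.4 literally would not be following Section 8.3.5.

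The filter that removes these events is a causality judgment. Section 8.3.3.2 gives it to the examining clinician, and Section 6.2 says that treatment assignment cannot be blinded. Control dyads do not receive RAMP, so relatedness to the intervention does not mean the same thing in the two arms. A summary filtered on it is hard to read by arm. At stake is whether the pilot's safety summary shows everything the protocol requires sites to collect.

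**Working it through.** The plan gives no figure to reproduce here, and no sample size, power or error rate enters. The check is a comparison of event sets.

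**Step 1: classify events.** Each AE is severe or not, serious or not, related or not: 2 × 2 × 2 = 8 combinations.

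**Step 2: read Section 9.4.4 both ways.** Reading A: intervention-related AEs, plus all SAEs. Reading B: intervention-related AEs and intervention-related SAEs.

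**Step 3: mark what each section covers.**

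| Severe | Serious | Related | Recorded (8.3.1, 8.3.4, 8.3.6) | To analysis (8.3.5) | 9.4.4, reading A | 9.4.4, reading B |
|---|---|---|---|---|---|---|
| yes | yes | yes | yes | yes | yes | yes |
| yes | yes | no | yes | yes | yes | no |
| yes | no | yes | yes | yes | yes | yes |
| **yes** | **no** | **no** | **yes** | **yes** | **no** | **no** |
| no | yes | yes | yes | yes | yes | yes |
| no | yes | no | yes | not named | yes | no |
| no | no | yes | yes | yes | yes | yes |
| no | no | no | no | no | no | no |
| **Total** | | | **7 of 8** | **6** | **6** | **4** |

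**Step 4: compare.**
- Reading A covers 6 of the 7 recorded combinations. The one lost is severe, non-serious, unrelated.
- Reading B covers 4 of 7. It loses that combination and both unrelated-SAE combinations.
- Section 8.3.5 includes the severe, non-serious, unrelated combination, which Section 9.4.4 misses under either reading. The conflict does not depend on how Section 9.4.4 is parsed.

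**Step 5: test the reading of Section 8.3.5.** The words for potential relatedness could govern severe AEs as well. Severe AEs would then be a subset of the potentially related AEs already named, and listing them would add nothing. Sections 8.3.1 and 8.3.4 list severe AEs as a separate category, and Section 8.3.4 follows them whatever their relationship. The reading used in the table fits better. Even under the narrower one, Section 9.4.4 still covers less than is recorded.

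**The case against.** The best defence is that Section 9.4.4 is an incomplete list and does not exclude anything. It contains no word such as only; Section 8.3.5 stands beside it as a commitment in its own right and does not promise a by-arm table. Sections 9 and 9.4.1 leave detail to the SAP, which was not available for this review. Both sentences could be carried out together. That is fair, and it limits the point to a conflict of wording. It does not remove it: Section 9.4.1 says the SAP will detail the analyses outlined in Section 9, and that outline names a narrower set than Section 8.3.5.

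It is also fair that severe events reach the reviewing IRB, the sponsor and the DSMB under Section 8.3.5, and that SAEs have their own route under Section 8.3.6. Oversight does not depend on the Section 9.4.4 table.

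A reader might go further and infer that stimulant side effects brought on by faster titration will disappear from the summary as unrelated. The protocol does not settle that. Section 8.3.3.2 makes an established alternate etiology a ground for Not Related, but makes a temporal relationship with the intervention a ground for Related. The same event can meet both. Such events might be lost or might be kept.

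A reader might also want an all-causality comparison between the arms. The protocol plans no safety comparison, and one would be affected by unequal ascertainment. Section 1.1 lists a medication side-effects query in the RAMP Report, and Section 8.3.4 says SAEs may come to light through RAMP Reports. AEs are otherwise not actively solicited (Sections 8.2 and 8.3.4), although providers are asked to remind caregivers to report them.

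**Conclusion.** The inconsistency is real. Section 9.4.4 omits severe, non-serious AEs judged unrelated, although they are recorded under Sections 8.3.1 and 8.3.4 and assigned to the analysis by Section 8.3.5. If relatedness is taken to govern both terms, it omits unrelated SAEs as well.

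The number of events affected is unknown. The protocol gives no AE rate, so any count would be arithmetic on an assumed rate. It is probably small: 36 dyads, about 3 months of follow-up each, no active solicitation, AEs and SAEs not expected (Section 8.2), and a definition of severe that lies close to two of the SAE criteria in Section 8.3.2.

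A reader might infer that the full-scale trial would be planned on a misleading safety table. The documents do not support this. Sections 3 and 9.4.2 tie that planning to engagement and utilization, and safety is neither an objective nor an endpoint.

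The conclusion assumes that severe AEs in Section 8.3.5 means severe AEs regardless of relationship, which is the better-supported reading. The correction is minor.

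**What to change.** Reword Section 9.4.4 so that its event set equals the recorded set. For example: *The DCOC will summarize descriptively, by arm, overall and by site, all recorded adverse events: all severe AEs and all SAEs regardless of relationship, and all AEs judged related to the study. Relationship, severity and seriousness will be tabulated for each event. No formal between-arm comparison will be made.*

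Add one sentence of caution: ascertainment may differ by arm because RAMP Reports include a side-effects query that controls do not receive. Keep the SAP's safety tables in line with the revised section.

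The cost is a sentence or two in the protocol and one or two table rows. The data are already to be collected, and nothing changes for sites or participants.

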#### 9.4.5 BASELINE DESCRIPTIVE STATISTICS

The statistical team will summarize baseline and demographic characteristics by intervention group and will apply summary statistics for both continuous and categorical variables. For continuous variables, descriptive measures will include number of non-missing values, mean, standard deviation, median, minimum, and maximum. For categorical variables, descriptive statistics will include frequency counts and proportions by category.

---

#### 9.4.6 PLANNED INTERIM ANALYSES

There are no planned interim analyses for this study.

---

#### 9.4.7 SUB-GROUP ANALYSES

No sub-group analyses will be performed.

---

#### 9.4.8 TABULATION OF INDIVIDUAL PARTICIPANT DATA

The statistical team will provide a detailed description of participant disposition, will tabulate the number of enrolled participants overall and by study site, and will present this data as counts and proportions. Additionally, the statistical team will summarize the number of participants either completing or discontinuing the study using counts and proportions.

---

#### 9.4.9 EXPLORATORY ANALYSES

We will use a Wilcoxon rank-sum test to compare the number of caregiver specific returned structured reports in each group. Additionally, we will repeat the same analysis for the number of teacher-specific returned structured reports in each group.

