The entire timeline will span 17 months with three phases. In the first phase of the study, the providers from the participating practices will receive ADHD Best Practices education and training in the portal use, and will be asked to provide informed consent. A member of the clinic staff (nurse, medical assistant or practice manager) will be identified as site champion. The site champion will facilitate communication between the site study team and the clinic staff. The second phase of the study will focus on child/caregiver and provider utilization. Providers will identify patients with a diagnosis of ADHD who are being started on stimulant medication to be contacted by study staff for enrollment. Research coordinators will discuss the study, perform eligibility screening and obtain consent (if deemed eligible by PI). The consented caregiver/child dyads will be randomized to intervention (requests to submit the RAMP Reports for 3 months) or control (usual care with attention control) groups. Families will be approached until 36 caregiver/child dyads are enrolled (only one child in a family may be enrolled). Each practice will have 6 weeks to enroll 9 participants. After the 6 weeks, practices with low enrollment will receive additional supports. Each week, progress to target will be evaluated to determine if any practice needs additional resources. If multiple practices do not meet enrollment goals, the study team may consider relaxing exclusion/widening inclusion criteria (ex. include patients undergoing re-titration, widen age criteria) and/or opening enrollment. Enrollment will be paused for 3 months from the last month of school to the start of the new school year (beginning of May to end of July). This will decrease the burden on practices and study staff during the time of the year with the fewest number of ADHD diagnoses. Once enrolled, caregiver/child participants will be randomized to either the intervention or control group and followed for approximately 3 months. Participants randomized to the intervention group will submit RAMP reports weekly for 4 weeks and then monthly for 2 months. Participants randomized to the control group will receive digital education handouts at the same frequency as the RAMP reports in the intervention arm. Research coordinators will periodically review the child participant's EMR and mark how many paper symptom assessments are returned while enrolled on the study for both groups. Research coordinators will also access the RAMP platform to log RAMP reports returned by caregivers/teachers, RAMP reports reviewed by providers, and provider survey results. All caregiver participants will complete a 90-day Vanderbilt Assessment as a retention measure (see section 1.2.1 for more details). This phase will continue until all 36 participants have completed their 3-month study period. In the third phase, the above endpoints will be calculated, the full-scale trial will be designed, and the findings presented in a manuscript.

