## 6.2 MEASURES TO MINIMIZE BIAS: RANDOMIZATION AND BLINDING

Following enrollment, caregiver/child dyads will be randomized into one of two treatment arms:

1. Intervention Arm: will participate in the RAMP for a period of 3 months
2. Control Arm: standard of care determined by the treating healthcare provider; digital education handouts (attention controls) distributed by the study team at the same intervals as the RAMP Report requests in the intervention group

Caregiver/child dyads who complete screening and enrollment procedures will be randomized using a stratified randomization scheme together with a varying permuted block randomization. Enrolled caregiver/child dyads from the practices will be randomly assigned to RAMP (intervention) or standard of care (control) at a 1:1 allocation ratio. Randomization will be stratified by practice (i.e., randomized within practices) to control for potential differences in study population or differences in management. Secure, practice-specific randomization lists will be generated for each site to use when randomizing a participant. At enrollment, the research coordinator will assign randomization assignments in sequential order, pulled directly from the list. Due to the nature of the intervention, it is not possible for blinding of treatment assignments to be performed in this study. All providers will receive Best Practice Education based on the 2019 AAP clinical practice guidelines, including the recommended frequency of for symptom gathering that is the basis for the planned schedule of RAMP Report requests. Therefore, providers caring for children assigned to the control group may attempt to meet this schedule. However, they will still face hardships inherent to paper forms.

Research coordinators will also make note if any paper symptom assessments are returned for the intervention arm in addition to the RAMP reports. A [study-specific assessment](#) will be done, at 90 days and will serve as a marker of retention.

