### 9.2 SAMPLE SIZE DETERMINATION

A total sample of 36 participants was agreed in accordance with published guidance for pilot studies. Up to 36 caregiver/child dyads and 20 providers will be enrolled. Our proposed sample size is also consistent with the recommendations of Whitehead and colleagues (2016). Their derived new stepped rules of thumb for a pilot trial sample size vary depending on an estimated standardized effect size for the main efficacy trial; therefore, if we assume a medium Cohen's effect (i.e.,  $0.3 \leq \delta \leq 0.7$ ) and 90% power for the main trial, a sample size of 36 participants with 18 randomized to each intervention arm in the pilot study is sufficient.

With a focus on participant recruitment and adherence, a sample size of 36 allows the study team to estimate an expected recruitment rate of 25% and adherence rate of 50%, each within 12-14 percentage points, with a confidence level of 90%. We expect the rate of return of the RAMP Reports to be a comparable rate to the general survey response rate of 52.7%, though it may be higher as the platform aims to function as an engagement tool.

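### The Wilcoxon tests in 9.4.9 ignore the practice strata used in randomization, and lose power if practices differ in a way that affects both arms

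*Protocol*

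**What the plan says.** Section 9.4.9 of the protocol fixes the test for caregiver reports: "We will use a Wilcoxon rank-sum test to compare the number of caregiver specific returned structured reports in each group". It continues: "we will repeat the same analysis for the number of teacher-specific returned structured reports in each group". Neither sentence mentions practice.

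Section 6.2 sets out the allocation: "Randomization will be stratified by practice (i.e., randomized within practices) to control for potential differences in study population or differences in management". The method is a "stratified randomization scheme together with a varying permuted block randomization", "at a 1:1 allocation ratio".

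On numbers, 9.2 holds that "a sample size of 36 participants with 18 randomized to each intervention arm in the pilot study is sufficient", and 4.1 sets the target per practice: "Each practice will have 6 weeks to enroll 9 participants". The protocol gives no significance level, power or expected effect for the two exploratory tests. Details of the analyses are deferred to a separate SAP (9 and 9.4.1), which is not at hand.

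**The concern.** The design treats practice as something that may affect the outcome and balances the arms within it. The test named in 9.4.9 then pools ranks over all four practices. Balancing within practice removes between-practice variation from the contrast between arms, but the null variance of the pooled rank-sum still contains it. When practices differ, the standard error is too large for the contrast it is paired with: the test rejects less often than its nominal level and misses real differences more often.

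This matters because 9.4.9 holds the only between-group tests that separate caregiver from teacher reports. Section 3 names caregiver and teacher engagement in each arm as important for planning the full-scale trial. With 18 dyads per arm there is little power to spare.

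**Working it through.** **The plan's own figures.** No power is stated for these tests, so there is nothing to reproduce for them directly. The one computable design figure, in 9.2, is 12-14 percentage points of precision at 90% confidence with n = 36. It reproduces: 1.645 × √(0.25 × 0.75/36) = 11.9 points and 1.645 × √(0.50 × 0.50/36) = 13.7 points. It does not bear on the choice of test.

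**Inputs from the protocol.** 36 dyads, 18 per arm, four practices, a target of 9 per practice, 1:1 allocation, permuted blocks within practice.

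**Assumed inputs (not in the protocol).** Block sizes 2 and 4; gamma-Poisson counts with dispersion 0.2; mean counts 1.5 (control) and 3 (intervention); between-practice SD on the log scale of 0.3, 0.5 and 0.7; two-sided 5% level.

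**Tests compared.**
- Unstratified: D = (rank sum in the intervention arm) − n₁ × (mean rank), ranks pooled over all practices; Var(D) = n₁n₀/(N−1) × (variance of the pooled ranks); z = D/√Var(D).
- Van Elteren: D and Var computed within each practice j from ranks inside that practice; z = Σ wⱼDⱼ / √(Σ wⱼ²Varⱼ), with wⱼ = 1/(nⱼ+1), here 1/10.

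**Power, 3,000 simulated trials per setting.** The Monte Carlo standard error is at most √(0.5 × 0.5/3000) = 0.9 points.

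| Between-practice SD | Effect shared by both arms: unstratified | Shared: stratified | Effect in control arm only: unstratified | Control only: stratified |
|---|---|---|---|---|
| 0.3 | 60% | 62% | 61% | 59% |
| 0.5 | 54% | 60% | 54% | 53% |
| 0.7 | 46% | 62% | 48% | 47% |

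With a shared effect the gain is 2, 6 and 16 points. With an effect in the control arm only there is none. A separate run of the shared-effect set-up gave lower levels but the same pattern: 58%, 49% and 42% unstratified against 59%, 57% and 56% stratified.

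**Size under no arm difference (both means 1.5, shared effect, 4,000 trials).** At SD 0.3, 0.5 and 0.7 the unstratified test rejects in 4.1%, 3.5% and 2.7% of trials; the stratified test in 4.9-5.2%.

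**No practice differences.** Power is about 64% unstratified and 61% stratified; another run gave 65% and 63%. Stratifying therefore costs 2-3 points.

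**A second outcome model, shared effect, 3,000 trials.** Counts are either binomial out of 6 requests (30% against 52.7%) or Poisson (1.5 against 3), both overdispersed.

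| Practice SD | Binomial power: unstratified / van Elteren | Poisson power: unstratified / van Elteren |
|---|---|---|
| 0 | 0.63 / 0.61 | 0.63 / 0.60 |
| 0.4 | 0.59 / 0.61 | 0.55 / 0.60 |
| 0.8 | 0.42 / 0.57 | 0.31 / 0.60 |

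At SD 0.8 the size of the unstratified test is 0.016 (binomial) and 0.010 (Poisson). At SD 0 both tests are near nominal (0.056-0.059). Uneven practices of 16, 10, 6 and 4 give the same picture (binomial, SD 0.8: 0.44 against 0.57). An aligned-rank test within practice has the same or slightly higher power than van Elteren.

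**Arms far apart.** Section 2.2 puts structured-report use at follow-up as low as 10%, and 9.2 expects RAMP return near 52.7%. Purely as an illustration, 6 requests × 10% = 0.6 and 6 × 52.7% = 3.2 reports. At those means both tests have at least 96% power for shared SDs from 0 to 0.7.

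**The case against.** The strongest objection concerns why practices would differ. A reader might infer that the provider-determined schedule for usual-care forms (1.1) makes the strata matter. That schedule acts on the control arm; RAMP requests are automated and follow a fixed timetable. The simulation shows no gain from stratifying when practices differ only in control returns. This part of the objection stands, so the case has to rest on differences shared by both arms. Such differences are plausible: practices may be rural and/or underserved, pediatric or family (1.1, 5.1), and 6.2 names study population as a reason for stratifying. The protocol does not quantify them.

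The assumed values also matter. Neither the control mean of 1.5 nor any between-practice SD is in the protocol. An SD of 0.7 implies about a four-fold ratio (e^1.4 ≈ 4.1) between practices one SD above and one SD below the mean. At 0.3-0.4 the gain is only about 1 to 5 points. This stands as a limit on size, not on direction.

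A reader might also take 9.4.9 to be the only place where caregiver and teacher engagement are separated. It is not: 9.4.2 summarises caregiver and teacher reports by group, and 6.3 tallies both sets of RAMP Reports. Those are descriptive; 9.4.9 holds the only between-group tests.

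Finally, strata for an exploratory rank test could be left to the SAP, which may yet add them. That is fair and lowers the severity. But 9.4.9 does name a test, and the one it names does not follow the randomization set out in 6.2.

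**Conclusion.** The point holds as a minor matter of efficiency. The unstratified test is conservative and loses power when practices differ in a way common to both arms: about 60% falling to 45% as the shared log-scale SD rises from 0.3 to 0.7, against about 61-62% with stratification, at assumed means of 1.5 and 3. The gain is negligible if only usual-care return varies between practices or if the arms are far apart, and there is a loss of about 2-3 points if practices are alike.

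A reader might go further and conclude that the planned tests are invalid or risk false positives. The calculations do not support that: the size is near or below nominal throughout. Nor does the protocol tie any decision to these tests.

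**What to change.** In 9.4.9, replace the rank-sum test for both the caregiver-specific and the teacher-specific counts with a van Elteren test using practice as stratum, or an aligned-rank test within practice. Report with each a practice-stratified difference between arms (for example a stratified Hodges-Lehmann estimate) and its 95% CI.

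The change is a line of text and uses standard methods. It needs no further data, since practice is already recorded for randomization. The price is the 2-3 points of power lost if practices turn out not to differ.
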